## Abstract

**Background:**

The composition of the gut microbiota both prior to and after haematopoietic stem cell transplantation (HSCT) is increasingly implicated in the outcomes of HSCT, including infections, poor immune reconstitution and disease relapse. Faecal microbiota transplantation (FMT) offers a potential strategy of supporting the gut microbiota and improve HSCT outcomes. Although FMT has been investigated in HSCT recipients, it has largely been evaluated therapeutically for indications such as infection, or once immunocompetency is regained.

**Methods:**

Peri-HSCT FMT (i.e. before and after HSCT) will be administered to eligible participants (adults undergoing autologous HSCT for a haematological malignancy) over two courses, with the first delivered immediately prior to conditioning and the second starting when ANC > 0.8. Following an open-label, safety run in (N = 5), peri-HSCT FMT will be evaluated for its efficacy in 51 participants, randomised 2:1 to FMT or placebo. The primary outcome is the proportion of participants who develop severe gastrointestinal toxicity defined by 3 consecutive days of severe diarrhoea (Bristol Stool Chart 6+), at a frequency of 4 + bowel movements/day within 3 weeks of HSCT. Safety is defined as the incidence of treatment-emergent adverse events (TE-AEs). Tolerability is defined as the incidence of TE-AEs and adherence to FMT.

**Discussion:**

The HSCT-BIOME study is a multi-centre, double-blind, randomised placebo-controlled trial designed to determine the tolerability, safety and efficacy of orally-administered encapsulated FMT to promote the stability of the gastrointestinal microenvironment for HSCT recipients. Peri-HSCT delivered FMT is hypothesised to promote microbial composition both before and following HSCT. Thus, the study will determine if administration of FMT post-HSCT during the neutropenic phase will enhance efficacy.

**Trial registration:**

ACTRN12624001104549. Date of registration: September 19, 2024 (prospectively registered).

## Background

Haematopoietic stem cell transplantation (HSCT) is a common treatment for haematological malignancies. It involves the use of high dose chemotherapy +/- total body irradiation (TBI), both of which serve to ablate the patient’s bone marrow, which is then reconstituted by infusion of stem cells collected from the patient (autologous HSCT) or a matched donor (allogeneic HSCT). Both auto- and allo-HSCT recipients experience a range of transplant related toxicities randing from infections, diarrhoea, mucositis, malnutrition, pain, to graft versus host disease (GvHD, allo-HSCT only) [1–3]. These require various interventions and treatment, which often serve to relieve symptoms but do not address the core biological drivers of these complications.

Recently, the contribution of the ecosystem of micro-organisms residing in the gastrointestinal tract – the gut microbiota – to HSCT complications has been increasingly recognised. Indicators of microbial disruption both before and after HSCT have been identified to predict a range of complications. For example, patients with low microbial diversity and high abundance of pathogenic microbial taxa were more likely to develop blood stream infections (BSI) after HSCT. In fact, the pre-chemotherapy gut microbiota was able to predict infection risk with a sensitivity of 90% [4]. Similarly, detrimental microbial attributes that are consistently reported in HSCT recipients (e.g. low diversity and pathogen expansion) have been identified to increase the risk of BSI, pulmonary infections, perturbed immune reconstitution, malnutrition, graft-versus-host disease and relapse [1, 5, 6].

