### Study objectives and outcome measures

**Table Taba:** 

Objectives	Outcome measures
Determine prophylactic efficacy of FMT on diarrhoea	Proportion of patients that develop severe diarrhoea determined by 3 consecutive days of BSC6 + at a frequency of 4 + bowel movements/day above baseline within 3 weeks of HSCT * Note: BSC and frequency will also be evaluated individually
Determine therapeutic efficacy of FMT on diarrhoea	Duration of severe diarrhoea defined as BSC6 + at a frequency of 4 + bowel movements/day above baseline
Determine clinical impact of FMT	Changes in body weight (kg) Incidence of fever (body temp > 37.8oC) Incidence of blood stream infections Use of supportive care interventions Duration of hospitalisation
Determine safety of FMT	Incidence of TE-AEs
Determine adherence to FMT administration	Number of capsules taken
Determine effect of FMT on mucosal barrier integrity	Plasma citrulline concentrations
Determine colonisation and function of donor FMT	Gut microbiota composition and diversity determined using bacterial genome sequencing on stool samples and SCFA analyses in plasma
Determine changes in symptom burden	ESAS-r-CS

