### Participants and study recruitment

The HSCT-BIOME trial will recruit eligible participants scheduled for conditioning chemotherapy prior to autologous HSCT for a haematological malignancy (Table 1).

This is a pilot study aiming to recruit N: 51 participants. This will adequately power the study to detect a 40% absolute reduction (80–40%) in the proportion of participants that meet the primary outcome of the study (alpha: 0.05, beta: 0.2, power 80%).

Potentially eligible participants will be identified at multidisciplinary team meetings (MDTs), hospital admissions and outpatient clinics The study will be introduced to the participant by their clinician, and provided with the PICF and the study will be introduced to the participant by their clinician. Between stem cell mobilisation and providing consent for their HSCT, participants will be given the PICF and consent will be collected at the same time as consenting for HSCT.

Once consented to the study, the participant is assigned a Study ID which will be used to identify all study material.

**Table 1 Tab1:** Inclusion and exclusion criteria

Inclusion	Exclusion
1. Age ≥ 18 years	1. Pre-existing gastrointestinal disease including Crohn’s disease, ulcerative colitis
2. Diagnosis of multiple myeloma, lymphoma or another haematological malignancy to be treated with auto-HSCT	2. Unable to swallow capsules
3. Scheduled to receive conditioning chemotherapy (+/- TBI) prior to auto- HSCT	3. Pregnancy
4. Able to provide written informed consent and follow all clinical trial related procedures (translator to be provided for people of culturally and linguistically diverse (CALD) backgrounds)	4. Nut allergy or anaphylactic food allergy
	5. Uncontrolled vomiting or oral mucositis that may impact swallowing (determined by participant) **
	6. Fever (body temp > 37.8oC) **

**Eligibility criteria to be reviewed before post-HSCT FMT intervention

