### Biospecimen collection

Stage 1: Faeces will be collected before and after FMT to confirm engraftment in the safety run in cohort..

Stage 2: Blood, saliva and stool (faeces) will be collected from participants longitudinally throughout the study. A maximum of 2 × 9 ml EDTA blood tubes and 2 × 9 ml SERUM (clotting) blood tubes will be collected at each timepoint. Saliva will be collected using ORAGENE-DNA OG-500 (self collection) tubes twice (sample 1: prior to starting FMT#1, sample 2: after FMT#1, prior to starting conditioning chemotherapy). will be collected using Zymo DNA/RNA shield tubes enabling self-collection by participants and easy transport in the registered mail.

See Table 4a,b for biospecimen collection schedule.

Blood will be collected at the following timepoints (+/- 2 days):

**Table 4a Tab4:** Blood collection schedule

Before starting FMT#1	Day of chemotherapy infusion	Day 0 (HSCT)	Post HSCT period	Day of discharge	Day ~ 35*
X	X	X	A maximum of 5x weekly aligning with routine blood draws	X	X

* Aligning with relevant clinic follow up appointment

Stool will be collected at the following time points (+/-2 day depending on the bowel habits of the participant):

**Table 4b Tab5:** Stool collection schedule

Before starting FMT#1	Day of chemotherapy infusion	Day 0 (HSCT)	Post HSCT period	Start of FMT #2	End of FMT#2	Day ~ 35*
X	X	X	A maximum of 5x weekly while and in-patient*	X	X	X

* If out-patient, participant will self-collect

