### Data analyses and synthesis

All qualitative data will be presented as descriptive data (e.g. participant demographics) and compared between groups using a Chi squared test. Study endpoints will be analysed as follows:

Effectiveness: Proportion of participants that meet the primary endpoint. This will be compared between the two arms using a Chi squared test.Safety: The incidence of all treatment-related AEs and SAEs will be compared between the two groups using a Chi squared test.Adherence: The proportion of participants that take all capsules. This will be compared between the two arms using a Chi squared test.Exploratory microbiota analyses: Uptake of the FMT will be determined by bacterial genome sequencing performed on faecal samples collected from participants.

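### The primary comparison is fixed as an unadjusted chi-squared test although randomisation is stratified and a pre-FMT stool sample is scheduled: the test is valid but gives up precision

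*Protocol article*

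**What the plan says.** All references are to the protocol article.

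- **Background**: "Indicators of microbial disruption both before and after HSCT have been identified to predict a range of complications". The outcomes it then ties to the microbiota are blood stream and pulmonary infection, immune reconstitution, malnutrition, GvHD and relapse. Diarrhoea appears in the list of transplant toxicities, but not among the outcomes said to be predicted. The only figure for predictive strength, a sensitivity of 90%, is for infection.
- **Abstract, Methods**: "peri-HSCT FMT will be evaluated for its efficacy in 51 participants, randomised 2:1 to FMT or placebo".
- **Participants and study recruitment**: "This is a pilot study aiming to recruit N: 51 participants", sized to "detect a 40% absolute reduction (80–40%) in the proportion of participants that meet the primary outcome", with "alpha: 0.05, beta: 0.2, power 80"%.
- **Randomisation**: stratified by site and by conditioning regimen, with no microbiota measure.
- **Biospecimen collection**: "Stool will be collected at the following time points", with a window of two days either side. Table 4b marks a sample before the first FMT course.
- **Study objectives and outcome measures**: "Gut microbiota composition and diversity determined using bacterial genome sequencing on stool samples". The Stage 2 outcome list makes this exploratory.
- **Data analyses and synthesis**: "Proportion of participants that meet the primary endpoint. This will be compared between the two arms using a Chi squared test". Neither stratification factor nor any baseline value enters this comparison.

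**The concern.** Two kinds of information that bear on the primary endpoint will be available and are left out of the test.

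The first is the pair of stratification factors. Someone judged site and conditioning regimen important enough to balance by design. An analysis that then ignores them does not use that balance: if they are prognostic, the unadjusted test tends to be slightly conservative and the interval wider than it need be. This mismatch is visible in the article alone and needs no outside assumption.

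The second is the baseline microbiota. It is the biological premise of the trial and is to be sampled before the first dose, but stratification does not balance it. With only 17 placebo participants the arms can differ noticeably by chance. If the measure is related to severe diarrhoea, the observed difference in the trial obtained will move with that imbalance.

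The choice has to be made before the data are seen. Adding a covariate after an imbalance is noticed would be a post hoc change to the primary analysis.

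**Working it through.** **1. The plan's own figure.** Inputs: 80% v 40%, alpha 0.05, power 80%, 2:1. Sidedness is not stated; two-sided is assumed, with pooled variance and no continuity correction.

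- Pooled rate = (0.8 + 2 × 0.4)/3 = 0.533.
- Placebo n = [1.96 × √(0.533 × 0.467 × 1.5) + 0.842 × √(0.16 + 0.24/2)]² / 0.40² = (1.198 + 0.445)² / 0.16 = 16.9, so 17.
- FMT n = 34 and the total is 51, as stated.
- Power at 17 v 34 is 80.3% by formula and 82.7% by exact enumeration of the uncorrected Pearson test.

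The sample size is therefore consistent with the unadjusted test.

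**2. How large a chance imbalance can be.** For a standardised baseline covariate, the SD of the difference between arms is √(1/34 + 1/17) = 0.297. An imbalance of at least 0.3 SD corresponds to |z| ≥ 0.3/0.297 = 1.01 (31% of trials), and at least 0.5 SD to |z| ≥ 1.68 (9%).

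**3. What an imbalance does to the observed risk difference.** The association with diarrhoea is not in the article, so the odds ratio (OR) per SD is an assumed range. To first order the shift is ln(OR) × p(1 − p) × imbalance. At p = 0.6 and 0.3 SD:

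- OR 1.5: 0.405 × 0.24 × 0.3 = 2.9 points
- OR 2: 0.693 × 0.24 × 0.3 = 5.0 points
- OR 3: 1.099 × 0.24 × 0.3 = 7.9 points

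Averaging over the covariate flattens the curve, and the fuller calculation gives 2.8, 4.5 and 6.3 points. At 0.5 SD it gives 4.7, 7.4 and 10.4 points. The planned difference is 40 points.

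**4. Power and type I error.** 6,000 simulated trials per setting, 34 v 17, one standard normal covariate, marginal rates held fixed. Pearson chi-squared is compared with a logistic score test adjusted for the covariate. The null has 60% in both arms.

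| OR per SD (assumed) | Power, unadjusted | Power, adjusted | Type I, unadjusted | Type I, adjusted | Type I unadjusted, imbalance > 1 SD of its distribution | Same, adjusted |
|---|---|---|---|---|---|---|
| 1 | 83.2% | 81.5% | 5.4% | 5.5% | 5.3% | 5.1% |
| 1.5 | 82.8% | 82.2% | 5.0% | 5.3% | 4.3% | 4.8% |
| 2 | 82.4% | 84.3% | 5.5% | 5.5% | 7.5% | 5.9% |
| 3 | 82.5% | 87.5% | 5.4% | 5.6% | 8.3% | 4.9% |
| 5 | 83.0% | 92.6% | 5.3% | 5.6% | 9.8% | 4.8% |

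Simulation error is about 1 point on power and 0.6 point on overall type I error. The conditional columns use about a third of the trials and are less precise; a separate run gave 6.4% at OR 1.5. The mean estimated difference at 80% v 40% was −0.40 at every OR, so the estimate is unbiased over randomisations.

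A second simulation with a likelihood-ratio test gave 82.6 v 82.8% (OR 1.5), 82.7 v 85.6% (OR 2) and 82.1 v 88.5% (OR 3). Across both methods the change is about 0, +2 to +3 and +5 to +6 points.

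**5. If FMT works as hypothesised.** The covariate is measured before FMT, and FMT is meant to change the microbiota before transplant. With the link to outcome absent in the FMT arm, power (chi-squared v adjusted) is 82.6 v 82.5%, 82.7 v 82.3% and 82.7 v 83.5% for placebo-arm ORs of 1.5, 2 and 3. The gain disappears. With the link only weakened (OR 1.5 on FMT, 3 on placebo) it is 82.9 v 85.0%.

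**6. Which adjusted method.** Assuming 2 sites and 3 regimens (neither count of strata is fixed by the article), a likelihood-ratio logistic model with arm, diversity and the design factors has type I error of 6.1–6.8%, against 5.3–5.6% for chi-squared. At OR 1 its power is 81.6% against 83.8%. Only 17 × 0.2 = 3.4 placebo non-events are expected, and near-separation occurs in about 2.5% of trials. A small-sample-safe method is therefore needed.

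**The case against.** The strongest case is that nothing here is an error. A randomised comparison by chi-squared test allows for chance imbalance, its type I error is close to 5%, and any unadjusted trial could be criticised this way for any baseline variable. This stands in large part. A reader might infer that an imbalance at 34 v 17 biases or invalidates the result; the calculations do not support that. Error rises only when one conditions on an imbalance in a covariate that is clearly prognostic.

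A reader might also infer that the article establishes baseline diversity as a strong predictor of severe diarrhoea. It does not. Its evidence concerns infection and other complications, and the trial's mechanism only presupposes a link with diarrhoea. Every gain from adjusting for diversity rests on an assumed OR, and it disappears if FMT removes the link in its own arm.

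Two smaller overstatements should also be avoided. A scheduled sample is not a guaranteed one, and the two-day window could place a baseline sample after dosing has begun. Nor is sequencing reserved for judging uptake of FMT: the Discussion foresees using the specimens to look for host and product attributes that determine response.

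Finally, adjusted and sensitivity analyses are commonly left to a statistical analysis plan, which is not shown. That is fair for supporting analyses. It does not fully answer the point, because the article itself names the primary test and that test has no place for the stratification factors.

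**Conclusion.** The point holds as a missed gain in precision, not as a flaw in validity. The firm part is that the design stratifies on two factors and the stated primary test uses neither. The article gives no prognostic strength for site or regimen, so no figure can be put on that gain.

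The weaker part is baseline diversity. Its value ranges from a loss of about 1–2 points of power if it is not prognostic, through nothing at OR 1.5, to about 5–6 points at OR 3. In trials with an imbalance beyond one SD of its distribution, adjustment brings a type I error of 7.5–8.3% (OR 2 to 3) back to 4.9–5.9%. These ORs are assumptions, and no diversity index is named. That supports a pre-specified supporting analysis, not a place in the primary model. The sample size of 51 need not change on this account.

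**What to change.** In Data analyses and synthesis:

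1. **Primary analysis.** Compare the arms on the primary endpoint with adjustment for site and conditioning regimen. State in advance how small strata are pooled. Use a method that is safe at this size, such as a stratified Mantel-Haenszel (CMH) test, or a logistic model tested by the score or Firth method. Report the standardised risk difference with a 95% CI. The unadjusted chi-squared test can be kept as supportive.
2. **One supporting analysis.** Add a single named alpha-diversity index as a continuous covariate. Take it from a stool sample confirmed to precede the first FMT dose. Give a participant without a usable sample the mean value plus a missing indicator.
3. **Blood stream infection.** Run the same supporting analysis for this secondary outcome, where the Background cites the association directly.

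The cost is analysis wording, the choice of one index and a pooling rule. Sampling and sequencing are already planned, but baseline sequencing must be finished before the supporting analysis; the primary result does not wait for it. Within that supporting analysis, about 1–2 points of power are lost if diversity is not prognostic.

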## Methods

### Study aims

Determine if encapsulated FMT reduces the proportion of participants that develop severe diarrhoea within 3 weeks of HSCT.Determine adherence to encapsulated FMT.Determine rates of FMT treatment emergent adverse events.

### Study objectives and outcome measures

**Table Taba:** 

Objectives	Outcome measures
Determine prophylactic efficacy of FMT on diarrhoea	Proportion of patients that develop severe diarrhoea determined by 3 consecutive days of BSC6 + at a frequency of 4 + bowel movements/day above baseline within 3 weeks of HSCT * Note: BSC and frequency will also be evaluated individually
Determine therapeutic efficacy of FMT on diarrhoea	Duration of severe diarrhoea defined as BSC6 + at a frequency of 4 + bowel movements/day above baseline
Determine clinical impact of FMT	Changes in body weight (kg) Incidence of fever (body temp > 37.8oC) Incidence of blood stream infections Use of supportive care interventions Duration of hospitalisation
Determine safety of FMT	Incidence of TE-AEs
Determine adherence to FMT administration	Number of capsules taken
Determine effect of FMT on mucosal barrier integrity	Plasma citrulline concentrations
Determine colonisation and function of donor FMT	Gut microbiota composition and diversity determined using bacterial genome sequencing on stool samples and SCFA analyses in plasma
Determine changes in symptom burden	ESAS-r-CS

### Trial design

To determine the safety and feasibility of peri-HSCT encapsulated FMT to improve outcomes of HSCT, the HSCT-BIOME Study will involve two stages:

Stage 1 – Safety run in: Open-label study in N: 5 participants to identify any TE-AEs and confirm adherence to the protocol. There will be a planned review by the Safety Monitoring Committee following Stage 1 to review outcomes and reported AEs before enrolment of participants in Stage 2 of the study.

Stage 2 – Efficacy trial: Double-blind, randomised, placebo-controlled trial to determine the clinical efficacy of the peri-HSCT encapsulated FMT.

### Patient and public involvement

Consumer representatives, identified through local advocacy group Cancer Voices SA, were consulted with respect to the design and implementation of this study. Specific design points dictated by consumers were the number of capsules deemed tolerable to take per day and methodology for data collection. Consumers provided input for all participant material, assisting with the phrasing of treatment side effects, FMT and other complexities of the trial to ensure it was accessible to a lay audience. Community organisations such as Leukaemia Foundation and Myeloma Australia will be involved to ensure these data are communicated with consumers.

### Study setting

Royal Adelaide Hospital, Adelaide, Australia.St Vincent’s Hospital, Sydney, Australia.

Further sites may be added once the trial has commenced. These will remain restricted to Australia.

All samples will be processed locally, but stored at the South Australian Health and Medical Research Institute or at BiomeBank (Adelaide, South Australia).

### Participants and study recruitment

The HSCT-BIOME trial will recruit eligible participants scheduled for conditioning chemotherapy prior to autologous HSCT for a haematological malignancy (Table 1).

This is a pilot study aiming to recruit N: 51 participants. This will adequately power the study to detect a 40% absolute reduction (80–40%) in the proportion of participants that meet the primary outcome of the study (alpha: 0.05, beta: 0.2, power 80%).

Potentially eligible participants will be identified at multidisciplinary team meetings (MDTs), hospital admissions and outpatient clinics The study will be introduced to the participant by their clinician, and provided with the PICF and the study will be introduced to the participant by their clinician. Between stem cell mobilisation and providing consent for their HSCT, participants will be given the PICF and consent will be collected at the same time as consenting for HSCT.

Once consented to the study, the participant is assigned a Study ID which will be used to identify all study material.

**Table 1 Tab1:** Inclusion and exclusion criteria

Inclusion	Exclusion
1. Age ≥ 18 years	1. Pre-existing gastrointestinal disease including Crohn’s disease, ulcerative colitis
2. Diagnosis of multiple myeloma, lymphoma or another haematological malignancy to be treated with auto-HSCT	2. Unable to swallow capsules
3. Scheduled to receive conditioning chemotherapy (+/- TBI) prior to auto- HSCT	3. Pregnancy
4. Able to provide written informed consent and follow all clinical trial related procedures (translator to be provided for people of culturally and linguistically diverse (CALD) backgrounds)	4. Nut allergy or anaphylactic food allergy
	5. Uncontrolled vomiting or oral mucositis that may impact swallowing (determined by participant) **
	6. Fever (body temp > 37.8oC) **

**Eligibility criteria to be reviewed before post-HSCT FMT intervention

